## Abstract

**Background:**

There is concern that existing models of acute hospital care will become unworkable as the health service admits an increasing number of frail older people with complex health needs, and that there is inadequate evidence to guide the planning of acute hospital level services. We aim to evaluate whether geriatrician-led admission avoidance to hospital at home is an effective alternative to hospital admission.

**Methods/Design:**

We are conducting a multi-site randomised open trial of geriatrician-led admission avoidance hospital at home, compared with admission to hospital. We are recruiting older people with markers of frailty or prior dependence who have been referred to admission avoidance hospital at home for an acute medical event. This includes patients presenting with delirium, functional decline, dependence, falls, immobility or a background of dementia presenting with physical disease. Participants are randomised using a computerised random number generator to geriatrician-led admission avoidance hospital at home or a control group of inpatient admission in a 2:1 ratio in favour of the intervention. The primary endpoint ‘living at home’ (the inverse of death or living in a residential care setting) is measured at 6 months follow-up, and we also collect data on this outcome at 12 months. Secondary outcomes include the incidence of delirium, mortality, new long-term residential care, cognitive impairment, activities of daily living, quality of life and quality-adjusted survival, length of stay, readmission or transfer to hospital. We will conduct a parallel economic evaluation, and a process evaluation that includes an interview study to explore the experiences of patients and carers.

**Discussion:**

Health systems around the world are examining how to provide acute hospital-level care to older adults in greater numbers with a fixed or shrinking hospital resource. This trial is the first large multi-site randomised trial of geriatrician-led admission avoidance hospital at home, and will provide evidence on alternative models of healthcare for older people who require hospital admission.

**Trial registration:**

ISRCTN60477865: Registered on 10 March 2014. Trial Sponsor: University of Oxford. Version 3.1, 14/06/2016.

**Electronic supplementary material:**

The online version of this article (doi:10.1186/s13063-017-2214-y) contains supplementary material, which is available to authorized users.

## Background

Older people are being admitted to hospital as an emergency in increasing numbers [1]. From a system perspective this trend is not sustainable, and from a patient perspective there are many reasons to question whether a hospital is the best place of care for older adults with frailty. There is some evidence to indicate that hospital care might be potentially harmful to older people due to a lack of mobility that can increase the risk of disability from frailty [2]. The high cost of hospital-based care has also been a major driver to innovate in an economic climate that does not allow for the expansion of hospital bed numbers to match the growth in admission numbers [3]. Avoiding admission to hospital by the provision of hospital-level care in the home is a model of healthcare that is being considered in many countries [4, 5] as hospitals deal with the rise in emergency admissions. However, the scale to which these models of care have transformed health systems is limited, reflecting the lack of evidence to underpin decision-making.

A meta-analysis of randomised trials of admission avoidance hospital at home is limited by the small number of small randomised controlled trials. The evidence suggests that these types of service, that include the option of transfer to hospital, may provide an effective alternative to inpatient care for a select group of older people who require hospital admission [4]. The lack of data on cost-effectiveness also limits the extent to which these types of service form part of a wider policy strategy for acute hospital-level care. It is possible that avoiding admission to hospital reduces the risk of delirium in older people who require hospital-level healthcare. Delirium, a frequent and serious complication in older people who develop an acute illness, is associated with adverse consequences which include increased risk of hospital-acquired complications, new admission to institutional care, new dementia, increased hospital length of stay and increased mortality [6, 7].

### Research objective

The primary objective is to undertake a multi-site randomised trial to estimate the effectiveness of geriatrician-led admission avoidance hospital at home in settings where health and social care provision vary. Secondary objectives are to investigate the incidence of delirium, mortality, new long-term residential care, cognitive impairment, activities of daily living, quality of life and quality-adjusted survival, length of stay, readmission or transfer to hospital, resource use (health and social care and informal care), costs and cost-effectiveness. We will also conduct a process evaluation to describe how the geriatrician-led admission avoidance hospital at home intervention is delivered, how this differs from inpatient care, and how health and social care provision varies between sites; this includes an interview study to explore the experiences of patients and carers.

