### Outcome measures

#### Primary outcome

We are collecting data for each patient on ‘living at home’, defined as the inverse of death or living in a residential care setting, at 6 months follow-up from randomisation.

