### Analysis

We will analyse the data using an intention-to-treat analysis and based on a mixed effect model adjusting for recruitment centre (random effects) and individual patient characteristics. For the primary outcome of living at home 6 months, the primary analysis we will use a mixed-effect logistic regression model including data available on all randomised patients at 6 months and 12 months follow-up, adjusting for recruitment centre, gender, and IQCODE score at baseline. In the model, participants and centres will be fitted as random effect, and time and treatment as fixed effect. We will fit an interaction term between time and intervention group so that possible differences of intervention effect could be assessed at each time point. Although, the method has the advantage of implicitly accounting for the data missing at random mechanism, we will also assess the impact of missing data on the primary analysis by carrying out sensitivity analyses based on imputing (multiple imputation) the missing values. We will use similar models for all binary outcomes (presence of delirium, cognitive impairment, etc.), and will use equivalent models for continuous outcomes (e.g. normal distribution). We expect length of stay to be highly skewed so other parametric models might be required for this, and in the case of poor fit we will use simple non-parametric tests (non-adjusted) for this outcome. We have planned one subgroup analysis of the effect of care setting (home versus hospital) on the incidence of delirium in people who are cognitively impaired (defined by the MoCA) [10].

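### The primary endpoint's available-data model is carried over to new residential care, Barthel and cognition at 6 months, which death precludes or leaves undefined; if mortality differs by arm, these comparisons can mislead in either direction

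*Protocol article*

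**What the plan says.** The primary outcome is living at home, "defined as the inverse of death or living in a residential care setting, at 6 months follow-up from randomisation". A death is therefore a failure, and every randomised participant with known status has a value.

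The Research objective and Secondary outcomes sections then list mortality, "new long-term residential care", cognition (MoCA) and activities of daily living (Barthel) as separate outcomes at 6 months. The Research objective section reads: "Secondary objectives are to investigate the incidence of delirium, mortality, new long-term residential care, cognitive impairment, activities of daily living".

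The Analysis section sets the model for the primary endpoint: "we will use a mixed-effect logistic regression model including data available on all randomised patients at 6 months and 12 months follow-up". It supports this choice by saying that "the method has the advantage of implicitly accounting for the data missing at random mechanism". It then extends the approach: "We will use similar models for all binary outcomes (presence of delirium, cognitive impairment, etc", and for scores it "will use equivalent models for continuous outcomes (e.g. normal distribution". It makes no exception for outcomes that death prevents.

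Three other places bear on the point. Table 1 schedules Barthel and MoCA at baseline and 6 months only. Data collection records death with its date, and place of residence at each follow-up visit. Among the planned analyses, only the QALY calculation under Economic analysis adjusts for mortality.

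**The concern.** The model suits the primary endpoint because death has a value there. It does not transfer cleanly to the other three outcomes.

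- **Barthel and MoCA-based cognition.** After death there is no score. This is not a hidden value that a missing-at-random argument could cover. The analysed set is the 6-month survivors, selected after randomisation.
- **New residential care.** Someone who has died cannot be in care. The protocol does not say whether such a person leaves the analysis or counts as a non-event. Either choice ties the result to mortality.

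The arm with fewer deaths retains people who are probably frailer and more likely to need residential care. Its survivors can look more dependent even if the service harmed nobody. These outcomes will be used to explain the primary result, in a frail, acutely ill population for whom the protocol names death as a risk in both arms. The Background section suggests that avoiding admission may reduce delirium, and links delirium to both mortality and institutional care. A mortality difference is therefore plausible here.

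**Working it through.** **The plan's own figures.** There is none to reproduce on this point. The Sample size section gives 12-month event rates of 50% and 40% but no death rate. Everything below except the planned 1350 participants and the 2:1 ratio is an assumption.

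**Set-up.** Suppose everyone who survives in the arm with more deaths would also survive in the other arm, and the treatment has no effect on residential care or function in these people. Let their residential-care risk be 10%. The arm with fewer deaths also contains extra survivors, with an assumed risk of 40% to 60%.

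**Formula.** Let S be survival in the arm with more deaths and S + d survival in the other arm. In the arm with fewer deaths:

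- residential care among all randomised = S × 0.10 + d × (risk in extra survivors)
- residential care among survivors = that figure ÷ (S + d)

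**Worked case, deaths 25% inpatient and 20% hospital at home (S = 0.75, d = 0.05).**

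- Extra survivors at 40%: 0.75 × 0.10 + 0.05 × 0.40 = 0.095; 0.095 ÷ 0.80 = 11.9%.
- Extra survivors at 60%: 0.75 × 0.10 + 0.05 × 0.60 = 0.105; 0.105 ÷ 0.80 = 13.1%.
- Inpatient: 0.75 × 0.10 = 0.075; 0.075 ÷ 0.75 = 10.0%.
- Living at home: inpatient 1 − 0.25 − 0.075 = 67.5%; hospital at home 1 − 0.20 − 0.095 = 70.5%, or 1 − 0.20 − 0.105 = 69.5%.

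All pairs below are inpatient v hospital at home.

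| Deaths | Risk in extra survivors | Residential care, survivors | Odds ratio (home v inpatient) | Residential care, all randomised, deaths as non-events | Living at home |
|---|---|---|---|---|---|
| 25% v 20% | 40% | 10.0% v 11.9% | 1.21 | 7.5% v 9.5% | 67.5% v 70.5% |
| 25% v 20% | 60% | 10.0% v 13.1% | 1.36 | 7.5% v 10.5% | 67.5% v 69.5% |
| 30% v 20% | 40% | 10.0% v 13.8% | 1.43 | 7.0% v 11.0% | 63.0% v 69.0% |
| 30% v 20% | 60% | 10.0% v 16.3% | 1.75 | 7.0% v 13.0% | 63.0% v 67.0% |
| 20% v 25% | 40% | 11.9% v 10.0% | 0.82 | 9.5% v 7.5% | 70.5% v 67.5% |
| 20% v 25% | 60% | 13.1% v 10.0% | 0.74 | 10.5% v 7.5% | 69.5% v 67.5% |

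In every row, under either handling of deaths, residential care points the opposite way from living at home. The last two rows show the reversal when hospital at home has more deaths.

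**Barthel.** Assume a mean of 15 in those who survive in either arm and 9 to 11 in the extra survivors.

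- Deaths 25% v 20%: (0.75 × 15 + 0.05 × 9) ÷ 0.80 = 14.62, a difference of −0.38; with 11 it is 14.75, or −0.25.
- Deaths 30% v 20%: (0.70 × 15 + 0.10 × 9) ÷ 0.80 = 14.25, or −0.75; with 11 it is 14.50, or −0.50.

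**Chance of a nominally significant difference against hospital at home.** Split 1350 at 2:1 into 450 and 900. Survivors number 450 × 0.75 = 337.5 or 450 × 0.70 = 315 (inpatient), and 900 × 0.80 = 720 (hospital at home). A simple two-sample calculation at two-sided 0.05, with full follow-up and no clustering, gives 14% to 30% for residential care with deaths of 25% v 20%, and 38% to 77% with 30% v 20%. For Barthel with an assumed SD of 4 to 6 the figures are 9% to 30% and 23% to 79%.

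**The case against.** The best defence is that a condensed article names a model family and leaves the handling of deaths to an analysis plan that is not shown. The protocol does not fix whether deaths are dropped or counted as non-events. That much stands, and the missing detail alone would not be a finding. What remains is the stated rule: one approach for all binary outcomes and its equivalent for continuous ones, with no exception. An analysis plan could repair this only by adding to or departing from that rule.

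It is also fair that much of the information will be reported. Mortality is its own outcome, the primary endpoint includes death, and QALYs allow for it. Home, residential care and dead exhaust the possibilities, so the first part of the fix is mainly presentation. With deaths as non-events, a higher residential-care proportion is a true description; it misleads only when read without the mortality result. This limits the seriousness but does not correct the survivor comparisons.

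A reader might infer that the plan fills in scores after death. The documents do not support this. Multiple imputation is tied to the primary analysis, and the missing-at-random remark follows the description of the primary model. With one post-baseline Barthel and MoCA measurement, the natural analysis compares observed survivors. Nor is cognition simply a continuous score: the Analysis section names cognitive impairment among the binary outcomes.

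**Conclusion.** The point holds. Applied as stated, the rule gives survivor-only comparisons for Barthel and cognition, and a residential-care comparison that depends on mortality whichever way deaths are handled. The arm with fewer deaths can look worse.

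The size rests on assumed death rates, care risks and Barthel means, and on there being no effect in those who would survive in either arm. On those assumptions, a 5-point mortality difference favouring hospital at home gives survivor odds ratios of 1.21 to 1.36 against it, and a 10-point difference gives 1.43 to 1.75.

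A reader might conclude that the bias is certain, or that it always runs against hospital at home. Neither follows. Without a mortality difference this mechanism produces no bias, and with more deaths under hospital at home it flatters that arm. Nor do the documents state that reducing mortality is an aim of the intervention; mortality is a secondary outcome. The primary endpoint is unaffected because it includes death.

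**What to change.** Amend the Analysis section for these three outcomes.

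1. **Residential care.** Report living at home, in residential care and dead together at 6 months, and at 12 months where collected, in all randomised participants with known status. Give the absolute difference by arm in each state. Use the primary endpoint's definition of residential care so that the states add to 100%. Read the residential-care result only alongside this table. In the first row of the illustration it would show +3.0 points at home, +2.0 in residential care and −5.0 dead for hospital at home, which does not invite a reading of harm.
2. **Barthel and cognition.** Keep the planned models but label their results as conditional on survival to 6 months. Add one supplementary analysis in all randomised participants that counts death as the worst outcome: ranked below the lowest score for a scale, or as failure for binary cognitive impairment. Survivors who miss the assessment remain ordinary missing data and should be kept distinct from deaths.

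The cost is analysis wording and one extra table. Death dates and place of residence are already collected, and the primary analysis, sample size and visit schedule do not change. The supplementary analysis mixes mortality with function and partly repeats the primary endpoint, so it should stand beside the survivor analysis and not replace it.

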## Methods/Design

The study protocol was developed using the SPIRIT (Standard Protocol Items: Recommendations for Interventional Trials) Checklist (see Additional file 1).

### Setting and sample

Participants are being recruited from primary care or an acute hospital-based assessment unit in Aneurin Bevan University Health Board; Bradford Teaching Hospitals NHS Foundation Trust; Guy’s and St Thomas’s NHS Foundation Trust, London; Royal Devon and Exeter NHS Foundation Trust; Monklands Hospital, NHS Lanarkshire; St John’s Hospital, NHS Lothian; Southern Health and Social Care Trust, Northern Ireland; Belfast Health and Social Care Trust, Northern Ireland. We are recruiting older people with frailty who require a hospital admission due to an acute change in health. This might be due to acute functional deterioration, delirium, falls and complex comorbidity. There is no simple accepted definition of this population due to variation in the acute presenting illness. However, it is agreed that the degree of prior disability is important and that attempts to define this group should be problem-based [8]. We will describe patients recruited to this trial according to functional dependence, cognitive impairment, comorbidity, history and/or presence of delirium and presenting complaint (such as falls, reduced mobility, confusion, carer strain).

### Eligibility criteria

We are recruiting patients who meet the following eligibility criteria for inclusion: (i) are 65 years and older, (ii) are willing and able to give informed consent for participation in the study, (iii) have been referred to the geriatrician-led admission avoidance hospital at home service and would otherwise require hospital admission for an acute medical event. The presence of a carer will not be a requirement for enrolment and will depend on the individual circumstances of the patient; this will be at the discretion of the clinician responsible for the patient, as is current clinical practice in each centre. Participants will be excluded if they have (i) an acute coronary syndrome (this includes myocardial infarction and unstable angina and is characterised by cardiac chest pain and associated with ECG changes), (ii) require an acute surgical assessment, (iii) have a suspected stroke, (iv) are receiving end of life care as part of a palliative care pathway, (v) refuse admission to the geriatrician-led admission avoidance hospital at home, or are considered by the clinical staff to be too high risk for home-based care, for example those who are physiologically unstable, who are at risk to themselves or if the carer reports hospital at home would not be acceptable, and (vi) patients living in a residential setting.

### Interventions

The intervention group is geriatrician-led co-ordinated, multi-disciplinary healthcare in the home for people who would otherwise be admitted to hospital (otherwise known as admission avoidance hospital at home). Members of the multi-disciplinary team (MDT) include nurses, physiotherapists, occupational therapists and social workers (who might be part of the primary health care team or dedicated staff). The MDT implements treatment and management recommendations, and if required refers to other services (e.g., older peoples’ mental health services, diagnostic services, social workers, dieticians, speech and language therapy, mental health services, pharmacy support and outpatient follow-up). Patients have access to inpatient care, general practitioners and the primary healthcare team. The use of intravenous infusions, administration of medication via a pump and 24-hour care is available in some sites. Healthcare is provided 7 days a week, admissions are restricted to Monday to Friday in all but one site, from 0900 to early evening, and emergency medical cover is available 24 hours a day.

The majority of participants (approximately 80%) who are randomised to inpatient care (the control group) will receive their care by a specialist-led geriatric service. This variation will reflect the challenges of real-life systems and continued pressure on beds. Measures, in the form of participating centres agreeing protocols, have been taken to ensure that the features of usual care are comparable.

### Outcome measures

#### Primary outcome

We are collecting data for each patient on ‘living at home’, defined as the inverse of death or living in a residential care setting, at 6 months follow-up from randomisation.

#### Secondary outcomes

At 6 months follow-up we are measuring:Incident and persistent delirium as defined by the Confusion Assessment Method (CAM). The CAM is a brief questionnaire that has been extensively used in research for screening and case ascertainment purposes [9].Cognitive impairment with the Montreal Cognitive Assessment (MoCA), the normal range is from 30 to 26 [10].Activities of daily living, measured by the Barthel Index [11].MortalityNew long-term residential careLength of stay in admission avoidance hospital at home and inpatient admissionReadmission or transfer to hospitalHealth status (measured by the EuroQoL five dimension (EQ5D) instrument to produce a single index value for use in cost-effectiveness analysis) [12]Resource usePatient satisfaction using the Patient-Reported Experience questionnaire, developed by Picker Europe and used in the National Audit of Intermediate Care [13].We are also collecting data for each patient on ‘living at home’ (the inverse of death or living in a residential care setting) at 12 months follow-up.

### Serious adverse event and adverse event reporting

The potential risks to participants of the research may include a fall (either in the home or inpatient setting), hospital-acquired infection for patients randomised to inpatient admission, hospital admission for those randomised to hospital at home, post-discharge hospitalization and death for all participants. We categorise an adverse event as serious if it results in death, is life-threatening, requires hospitalisation or prolongation of existing inpatient hospitalisation, results in persistent or significant disability or incapacity, or is an important medical event. Expected events for this patient population include falls, pressure sores, hospital or community-acquired infection and transfer to hospital. All serious adverse events (SAEs) which are related to administration of any of the research procedures, and are an unexpected occurrence, either observed by the recruiting clinician or reported by the participant, will be recorded on the case report form (CRF), and forwarded by the site to the trial manager following assessment for seriousness by the site clinician. As a minimum, the following information will be recorded: description, date of onset, end date, assessment of relatedness to the geriatrician-led admission avoidance hospital at home intervention, other attribution/co-intervention and action taken. Follow-up information will be provided as necessary. The chief investigator (CI) or delegate will report SAEs, which in the opinion of one of the clinical leads are ‘related’ and ‘unexpected’ when relating to the study procedures, to the Research Ethics Committee (REC) within 15 working days of the CI becoming aware of the event.

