### Data collection, management and analysis

Research nurses at each site collect data from participants, and from their caregivers if the caregiver is the designated consultee, at baseline and 6 months after randomisation and at 12 months for the primary outcome, with the exception of an assessment of delirium which is at 3 and 5 days, and at 1 month after recruitment (Fig. 1). Each site completes a form to record if death has occurred, with the date; these data are collected from the medical records. Place of residence is recorded by the research nurses at each follow-up visit. Data are collected using a paper form, or directly to an electronic pro forma on Open Clinica.

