**Fig. 2 Fig2:**
[figure not shown]
Participant timeline

At the 6-month follow-up point we collect data from all patients on mortality, new long-term residential care, cognitive impairment, activities of daily living, quality of life, length of stay, readmission or transfer to hospital, and on the number, type and duration of hospitalisations, the use of outpatient and day-case services, the use of community-based health care services including general practitioner consultations and practice-based nursing, medications, respite care, social care including admission to residential or nursing home, and amount of informal care received over the preceding 6 months. Unit costs will be attached to these resource volumes, using National Health Service (NHS) reference costs, Unit Costs of Health and Social Care (PSSRU), and other national data sources. We will collect the costs of the admission avoidance hospital at home intervention in collaboration with providers, and include training time and other elements. This is likely to vary between centres and we aim to collect cost information from all participating centres if possible. At 12 month follow-up we will collect data on living at home (Table 1).

**Table 1 Tab1:** Case report form

	Study period					
	Baseline	Day 3	Day 5	1 month	6 month	12 month
ENROLMENT						
Eligibility screen	X					
*Informed consent*	X					
*Screening log*	X					
Randomisation	X					
ASSESSMENT						
Assessment form	X	X	X	X	X	X
*Demographics*	X					
*Presenting problem*	X					
*Place of assessment*	X	X	X	X	X	X
*Patient status* (*‘living at home’*)		X	X	X	X	X
*Subsequent admissions*				X	X	
Adverse event log		X	X	X	X	X
QUESTIONNAIRES						
Barthel Index of Activities of Daily Living	X				X	
Confusion Assessment Method (CAM)	X	X	X	X		
Charlson Co-morbidity Index	X				X	
Health Service Use Questionnaire	X				X	
Short Form of the Informant Questionnaire on Cognitive Decline in the Elderly (Short IQCODE)	X					
Montreal Cognitive Assessment (MoCA)	X				X	
EuroQol five-dimension five-level (EQ-5D-5 L)	X				X	
Patient feedback form				X		
Difficulties in Questionnaire completion Form	X	X	X	X	X	
MISCELLANEOUS						
Death form	Completed on patient death					
Discontinuation form	Completed when a patient withdraws or is lost to follow-up					

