#### Study oversight

The overall supervision of the trial is carried out by the Trial Steering Committee. An independent Data Monitoring Committee meets every 6 months to review trial progress and data, this includes all SAE reports. The sponsor is the University of Oxford.

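### The ethics-reporting filter (related and unexpected) also decides which SAEs are recorded, leaving serious falls, pressure sores and infections with no defined, equal route in both arms

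*Protocol article*

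**What the plan says.** The section on serious adverse event and adverse event reporting does four things that bear on this point.

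- It names risks: falls in either setting, hospital-acquired infection in the inpatient arm, hospital admission in the home arm, and later hospitalisation and death in both.
- It lists what is to be regarded as expected: "Expected events for this patient population include falls, pressure sores, hospital or community-acquired infection and transfer to hospital".
- It sets the recording rule: "All serious adverse events (SAEs) which are related to administration of any of the research procedures, and are an unexpected occurrence" go on the case report form and are forwarded by the site. The minimum content of that record includes an "assessment of relatedness to the geriatrician-led admission avoidance hospital at home intervention" and a field for other attribution or co-intervention.
- It applies the related-and-unexpected test again, to decide which SAEs go to the Research Ethics Committee within 15 working days.

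Elsewhere, the Study oversight section says: "An independent Data Monitoring Committee meets every 6 months to review trial progress and data, this includes all SAE reports". Table 1 schedules an "Adverse event log" at day 3, day 5, 1 month, 6 months and 12 months. The Economic analysis section lists adverse events among the resource-use data. On deaths, the data collection section says: "Each site completes a form to record if death has occurred, with the date". The secondary outcomes include mortality, readmission or transfer to hospital, and length of stay. They do not include falls, pressure sores or infections.

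**The concern.** A filter for expedited reporting answers a narrow question: which events must an ethics committee hear about quickly? It is a poor rule for deciding what a trial records, because it removes the foreseeable events. In a comparison of care settings for frail older people, the foreseeable events are the ones that may differ between home and hospital.

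The test also depends on a judgement of relatedness made at the site in an open trial. The stated relatedness field refers to hospital at home and has no stated counterpart for inpatient care. A harm arising from the control setting is therefore not clearly invited onto the form in the way that a harm of the home setting is.

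Two things are at stake: whether the DMC sees these harms by arm while recruitment continues, and whether the final report can compare them. Events not recorded as they happen are hard to recover later without bias.

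**Working it through.** No arithmetic applies. The check is to follow each event type through the text and then to set the passages side by side.

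**1. The recording rule applied to the section's own list of expected events**

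| Event type classed as expected | Meets the SAE recording rule? | Named as a risk in the same section? | Compared by arm through a listed outcome? |
|---|---|---|---|
| Falls | No (expected) | Yes | No |
| Pressure sores | No (expected) | No | No |
| Infection, hospital- or community-acquired | No (expected) | Yes, for hospital-acquired | No |
| Transfer to hospital | No (expected) | Yes, as admission in the home arm | Yes, secondary outcome |

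All four types fail the rule as written. One has a substitute among the listed outcomes, and three do not. Death is also a named risk, and it is covered separately by the death form and by mortality as a secondary outcome.

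**2. The rule against its own form.** Entry requires relatedness to research procedures. Once an event is entered, the form assesses relatedness to the hospital at home intervention and any other attribution. These are different tests. A harm of the care setting need not be a harm of a research procedure, so it could fail at entry although the form has a field meant for it. An attribution field is also most useful if events not already judged related are being recorded, which the entry rule does not provide for.

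**3. The rule against Table 1.** The log is scheduled at five visits and its content is not stated. The only recording rule in the section that covers adverse events is the restrictive one. A site following that rule would leave most foreseeable events off the log, and a site following the table might enter them all. Capture could then differ between sites.

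**4. The rule against the Economic analysis.** Adverse events are listed there as resource-use data. The list of data collected at 6 months, in the data collection section, does not include them. The costing therefore presupposes a source that the recording rule does not supply.

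**5. Whether hospitalisation data can stand in.** The number, type and duration of hospitalisations, transfers and length of stay are collected in both arms. As a proxy for falls or infections they are uneven. A serious event at home may show as a transfer, whereas the same event during the control arm's index admission produces no transfer and at most a longer stay. The proxy also does not identify the cause.

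**6. What reaches the DMC.** The DMC is to "review trial progress and data, this includes all SAE reports". SAE reports are the only safety input named. By step 1, those reports would not contain serious falls, pressure sores or infections, unless a site treated a particular event as both unexpected and related to research procedures.

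**The case against.** The strongest reply is that the rule governs SAEs placed on the form and forwarded, and does not say that other events go unrecorded. Table 1 has a separate log at five visits, and no sentence ties that log to the SAE filter. Adverse events are to be costed, which makes little sense if almost none are captured. The DMC reviews trial data generally, not SAE reports alone. The consequences that make an event serious (death, hospitalisation, prolonged stay, lasting disability) are largely visible in outcomes collected for everyone: mortality, transfers, length of stay, the Barthel Index and new residential care. And this is a condensed article, so the full protocol may define the log and the safety tables.

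Much of this stands, and it rules out several stronger readings that a reader might infer:

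- *That falls, pressure sores and infections are never recorded.* The log and the costing list leave open that they are.
- *That the DMC would see almost nothing.* Its remit is wider than SAE reports.
- *That a control-arm harm could never qualify.* The entry test refers to research procedures without naming an arm, and the form has a field for other attribution.
- *That the trial could say nothing about safety.* Deaths, transfers, hospitalisations and length of stay are collected in both arms.

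The reply does not dispose of the rule itself. It is stated in the article, not left to another document, and it conflicts with other stated parts of the plan. The outcomes listed in reply show consequences without causes, and for transfers they do so unevenly between the arms.

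**Conclusion.** The point holds in a limited form. The related-and-unexpected test, suited to ethics committee reporting, is also the stated rule for recording and forwarding SAEs. Followed as written, it keeps serious falls, pressure sores and infections out of the SAE reports that the DMC is to review, although two of these are named as risks and none is a secondary outcome. It is not reconciled with the adverse event log, with the adverse events in the economic analysis, or with a relatedness field that refers to hospital at home and has no stated inpatient counterpart.

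The effect is confined to cause-specific harms, that is, three of the four event types classed as expected. The documents give no rates for these events, so the number affected cannot be stated, and the conclusion does not need it. The primary outcome is untouched.

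The conclusion assumes that sites apply the recording sentence literally and that no guidance outside the article widens the log. If such guidance exists, what remains is to bring the article's passages into agreement with it. The change is worth making because it is cheap and improves both monitoring and the comparison of harms by arm.

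**What to change.** Reconcile the adverse event section, Table 1, Study oversight and the Economic analysis as follows.

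- Record every SAE, and all falls, pressure sores and infections, in the existing adverse event log, in both arms on the same schedule, regardless of relatedness or expectedness.
- Assess relatedness to the allocated care setting, home or inpatient, in both arms, and use the same wording in the rule and on the form.
- Tabulate these events by arm for the DMC and in the results, and state that the log is the source for the adverse events that are costed.
- Keep the related-and-unexpected test solely as the filter for reporting to the ethics committee.

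The cost is a protocol amendment, revised guidance for completing the case report form, and some extra data entry at sites. No new visit or form is needed. Because recruitment is ongoing, the report should state the date from which the wider recording applied, as earlier participants may have less complete data.
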